### Data management

The research team will design a data management guideline to protect the privacy and confidentiality of the participants without the need for a data monitoring committee given the study’s low risk and minimal safety concerns. All participants’ personal identification information will be removed and replaced by a new ID prepared by the research team. All the collected data will be stored in a stand-alone server with a secure encryption system managed by a technician to prevent data leakage and improper use. The dataset will not be publicized and access to the interim and final study dataset will be limited to the prinicipal investigator and the research team. If any team members wish to retrieve, export or analyze the data, they must obtain permission from the higher-ups and operate on a pre-approved, designated computer. In addition, all paper records and documents will be stored in a centralized location.

### Data analysis

The research team will use descriptive analysis to summarize the socio-demographic characteristics of the general participants and various subgroups, HIV related knowledge, physical and mental health status, attitudes toward HIV, and lifestyle habits such as condom and drug use. The team will compare the baseline data between the intervention groups and the control group to measure the equivalence of the characteristics at baseline by using a t-test, and chi-squared-test and calculating the standard difference.

To investigate the effect of the mobile-based HIV-related message intervention, the team will use a t-test and chi-squared test to compare the significance of the intervention-related difference between groups at 6-, 12-, and 18-months. Since the outcomes are measured using numerical values (e.g., HIV-related knowledge, scores from 1 to 100), binary values (0,1) and categorical types (e.g., level of engagement, ranges from 1 to 6), different regression models (ordinary least squares, generalized linear mixed models) will be used for analysis according to the unique circumstances. Finally, sub-analysis will be conducted for the different age, gender, and education groups to explore the evidence of the effects related to various characteristics.

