#### Villagers’ baseline questionnaire

Participants and their family members will complete the baseline questionnaire in person during the enrollment procedure using the online data-collecting application Interviewer. The questionnaire will be filled out in person because many local villagers are illiterate in Mandarin Chinese, and unable to fill out the questionnaire independently without the staff’s assistance.

The framework of the questionnaire includes the following: (1) Questions on HIV-related knowledge. One of the study’s primary purposes is to measure changes in HIV-related knowledge levels among residents in Liangshan. To achieve this goal, the research team designed a new questionnaire, the HIV Related Knowledge Scale, by integrating questions from the HIV Treatment Knowledge Scale and the HIV-KQ-18 Knowledge Scale to assess the participants’ comprehension of HIV-related facts, key populations, transmission, symptoms, testing options, treatments, laws, and harmful consequences. (2) Financial information such as the family’s monthly medical and living expenditures, income level, insurance information, and savings. (3) Villagers’ additional information. This includes their demographic information (e.g., marital status, education, and current occupation), clinical characteristics (e.g., blood pressure, opportunistic infections, and height/weight/body mass index), mental health, quality of life, and stigma toward HIV (Table 1).

**Table 1 Tab1:** Outcome measures and corresponding questionnaires

Outcome	Measure	Baseline survey	Follow-up survey
Prevention			
HIV knowledge	HIV Treatment Knowledge Scale [46], HIV-KQ-18 knowledge scale [47]	X	X
Condom use	Condoms use self-efficacy scale (CUSES) [48]	X	X
Substance use	Alcohol, Smoking, and Substance Involvement Screening Test (ASSIST) [49], Drug Abuse Screening Test (DAST-10) [50]	X	X
Health outcomes			
Clinical characteristics (BMI, opportunistic infections, blood pressure)	Original measure	X	X
HIV prevalence	Regional data	X	X
Mental health	Primary Care Evaluation of Mental Disorders (PRIME-MD) patient questionnaire [51]	X	X
Quality of life	EQ-5D [52]	X	X
All-cause mortality	Regional data	X	X
Social factors			
Stigma towards HIV	Internalized AIDS-Related Stigma Scale [53]	X	X
Social support	Medical Outcomes Study Social Support Survey (MOS-SS) [54]	X	X
Evaluation of intervention and doctor			
Secondary transmission of knowledge	HIV Treatment Knowledge Scale [46], HIV-KQ-18 knowledge scale [47]	X	X

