### Follow-up surveys

Follow-up assessments, identical to the baseline questionnaires, will be scheduled at 6, 12, and 18-month periods. The participants and their family members will be offered financial compensation of 20 CNY for their completion of the questionnaires at the designated times.

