### Randomization and allocation

Randomization is done by the research team at the cluster level using a stratified randomization method, with each village defined as a cluster. First, each village will be assigned a number. Next, the cillage numbers will be extracted and randomized into three groups in a 1:1:1 ratio: (1) The “Control” group without any mobile-based message intervention; (2) “Intervention A” with village doctors delivering HIV-related intervention messages to the participants and receiving a standardized monetary compensation, and (3) “Intervention B” with village doctors delivering HIV-related intervention messages to the participants and receiving a monetary compensation, the amount of which will depends on how well the participants perform during the intervention.

In the entire process of data collection, management, and analysis, the staff members will not be informed of the randomization scheme. The data analyst will also not be informed until the results of the analysis obtained. Only the research team staff responsible for message delivery will be aware of which villages are assigned to each experimental group. The village doctors will not know the experimental group to which they belong or the differences between the three groups; this will prevent them from comparing their responsibilities, tasks, and monetary compensation with others in a different group, which could result in bias or a change in attitude toward their assignment. Furthermore, the village doctors will not be allowed to discuss with the participants of any group information about which the doctors have speculated.

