### Outcomes measures

#### Primary outcomes

One of the study’s primary outcomes is HIV-related knowledge improvement, which is obtained by calculating weighted scores for the indicators in the HIV Related Knowledge Scale to represent the participants’ and their family members’ level of knowledge measured by the baseline and follow-up questionnaires. The research team will compare the control group and the two intervention groups to investigate whether the groups receiving the mobile-based HIV-related health education develop a deeper understanding of HIV-related knowledge than the control group which did not receive the intervention. For the second primary outcome, the research team will compare “Intervention A” and “Intervention B” to determine what type of financial reward, standardized compensation or participant performance-based compensation, is more effective at incentivizing village doctors to deliver and promote the content of the intervention. The difference between the cost-effectiveness and the participants’ HIV-related knowledge improvement of the two groups will be used to evaluate which intervention yields a more effective outcome.

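### The effect tests that the protocol names cannot use the baseline knowledge score or the strata: make a baseline-adjusted mixed model primary and drop the baseline significance tests

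*Protocol article*

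**What the plan says.** All references are to the protocol article; no separate analysis plan is at hand.

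- **Effect of the intervention (Data analysis).** "the team will use a t-test and chi-squared test to compare the significance of the intervention-related difference between groups at 6-, 12-, and 18-months".
- **Further models (Data analysis, next sentence).** "different regression models (ordinary least squares, generalized linear mixed models) will be used for analysis according to the unique circumstances". No covariates are listed, and neither the tests nor the models are called primary.
- **Baseline comparison (Data analysis).** The arms are compared "to measure the equivalence of the characteristics at baseline by using a t-test, and chi-squared-test and calculating the standard difference".
- **Baseline measure of the outcome (Follow-up surveys).** "Follow-up assessments, identical to the baseline questionnaires, will be scheduled at 6, 12, and 18-month periods". Each participant followed up therefore has a baseline knowledge score on the same instrument.
- **Primary outcome (Primary outcomes).** Knowledge improvement, from the "level of knowledge measured by the baseline and follow-up questionnaires". This may mean a change score, but the text does not say so. The second primary outcome compares Intervention A with Intervention B, partly on the same knowledge measure.
- **Randomisation (Randomization and allocation).** Done "using a stratified randomization method, with each village defined as a cluster". The stratification factors are not named.

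**The concern.** A two-sample t-test or a chi-squared test has no place for a covariate. If those tests are the main analysis, the strongest likely predictor of follow-up knowledge, the participant's own baseline score, is left out or enters only by subtraction. The strata used in the randomisation are left out as well. Both are available at no extra cost, so any precision they offer would be given up for nothing. This affects both primary comparisons.

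The baseline tests are a second, smaller matter. A non-significant result does not show that arms are equivalent. Under sound randomisation, a significant one reflects chance. The tests therefore do not answer the question set for them, and the standardised difference planned beside them already describes balance.

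**Working it through.** **1. The plan's own figure (Sample size calculation).** Inputs: 66 clusters and 1,056 participants per arm, 80% retention, 20 per cluster, two-sided alpha 0.05, power 90%.

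- 1,056 / 66 = 16 retained per village, and 16 / 0.8 = 20 enrolled.
- 1,056 / 0.8 = 1,320 per arm, and 1,320 × 3 = 3,960. This matches the stated total.

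The 66 clusters cannot be re-derived, because no effect size, standard deviation or intracluster correlation (ICC) is given. Below, the 90% is assumed to belong to an unadjusted comparison of follow-up scores.

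**2. Formulas.** Let r be the baseline-to-follow-up correlation (not in the article; assumed), with equal variance at both times. Relative to a follow-up-only comparison (variance 1):

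- baseline-adjusted: 1 − r²
- change score: 2(1 − r)
- adjusted relative to change: (1 − r²) / [2(1 − r)] = (1 + r)/2
- power = Φ[(1.960 + 1.282)/√(variance ratio) − 1.960]

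**3. Results.**

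| r (assumed) | Adjusted / follow-up only | Change / follow-up only | Adjusted / change | Power, adjusted | Power, change score |
|---|---|---|---|---|---|
| 0.3 | 0.91 | 1.40 | 0.65 | 92.5% | 78.2% |
| 0.4 | 0.84 | 1.20 | 0.70 | 94.3% | 84.1% |
| 0.5 | 0.75 | 1.00 | 0.75 | 96.3% | 90.0% |
| 0.6 | 0.64 | 0.80 | 0.80 | 98.2% | 95.2% |
| 0.7 | 0.51 | 0.60 | 0.85 | 99.5% | 98.7% |

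Example at r = 0.5: 3.242/√0.75 − 1.960 = 1.783, and Φ(1.783) = 0.963.

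**4. How far a single r can mislead.** With villages as clusters, the gain depends on two correlations. Illustration, all values assumed: ICC 0.05, 16 retained per village, within-village r = 0.5, village-level r = 0.2.

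- Variance of a village mean, unadjusted: 0.05 + 0.95/16 = 0.1094.
- Each part adjusted by its own correlation: 0.05 × (1 − 0.04) + (0.95/16) × (1 − 0.25) = 0.0480 + 0.0445 = 0.0925.
- Ratio: 0.0925/0.1094 = 0.85. Power is about 94%.

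This treats the true village baseline mean as known. With only the observed village mean, the correlation of village means is (0.2 × 0.05 + 0.5 × 0.95/16)/0.1094 = 0.363. The ratio is then 1 − 0.363² = 0.87, again with about 94% power. The single-r formula at 0.5 gives 0.75 and 96.3%. A higher village-level correlation would give a larger gain.

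**5. Baseline tests.** With 20 independent valid tests at 0.05 (the number is assumed), 20 × 0.05 = 1.0 significant result is expected, and the chance of at least one is 1 − 0.95²⁰ = 64%. If the tests also ignore villages, the design effect with 20 per village is 1 + 19 × ICC. For an assumed ICC of 0.01, 0.05 and 0.10 it is 1.19, 1.95 and 2.90. The false-positive rate, 2[1 − Φ(1.960/√design effect)], is then about 7%, 16% and 25%.

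**6. Strata.** The factors are unnamed, so no gain can be computed.

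**The case against.** The strongest reply is that the article does plan regression. Ordinary least squares and generalized linear mixed models can carry the baseline score, the strata and a village effect. An article commonly leaves covariate lists to the full analysis plan, which is not shown. The outcome is also called improvement, so the baseline score may already enter through a change score.

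Most of this stands, and it rules out several stronger readings:

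- **That the arm comparison is unadjusted, or that baseline is ignored.** A reader might infer this from the t-test sentence alone. The documents do not support it: covariates in the models are unspecified, not excluded, and a change score uses baseline, though less efficiently.
- **That the effect estimate would be biased.** In a randomised comparison, omitting the baseline score costs precision only.
- **That omitting the strata makes the test too liberal.** It usually makes the standard error conservative.
- **That a particular gain, such as 25% of the variance, belongs to this trial.** It follows from an assumed r. Likewise, the article gives no expected difference between A and B.
- **That the baseline tests distort the results.** No stated decision depends on their p-values. Describing baseline balance is itself useful, since the article does not fix whether participants are enrolled before or after their village is allocated.

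The reply does not remove the point. The article commits to covariate-free tests for the effect and sets them beside the models without ranking them. The change-score reading does not close the gap either, because adjustment has the lower variance at every r in the range. The reply also leaves untouched the use of significance tests to establish equivalence.

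**Conclusion.** The point holds as a free improvement in precision, not as a threat to validity. The effect tests named cannot use the baseline score as a covariate or the strata, and the models that could are neither specified nor made primary. For an assumed single r of 0.3 to 0.7, the adjusted variance is 9% to 49% below that of a follow-up-only comparison, or 35% to 15% below that of a change-score comparison. The power figures further assume that the stated 90% refers to an unadjusted follow-up comparison. The direction is secure. The size is not, because it depends on village-level and within-village correlations that the article does not give. The gain from the strata cannot be quantified.

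The baseline t-tests and chi-squared tests cannot do what they are planned for, but their consequence is small. Whether the effect t-test allows for villages is a separate question on which this point does not rest.

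**What to change.** In Data analysis:

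1. Replace the t-test and chi-squared test of the effect with one named primary analysis for every between-arm comparison, including A versus B. This should be a mixed model with a village effect and, as fixed covariates, the participant's baseline knowledge score (optionally also the village mean baseline score) and the stratification factors.
2. Name the stratification factors in Randomization and allocation so that the model can be written down.
3. Delete the baseline t-tests and chi-squared tests. Keep the descriptive summaries and the standardised differences.

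The cost is wording and analysis code. The baseline scores are already to be collected and the strata are fixed by the randomisation, so no extra data, visits or participants are needed.

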### Sample size calculation

The intervention and control groups are of equal size, and two-tailed hypothesis testing is assumed. The sample size is calculated using the Stata software CRCT sample size function. By setting the power = 90%, α = 0.05, and desired confidence level = 95%, the number of clusters per arm is 66, and the sample size of each arm is 1,056. Assuming a retention rate of 80% during follow-up, 20 participants are needed for each cluster, totaling 3,960 participants for the entire study.

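### The knowledge effect is tested separately at each visit; one mixed model over all visits would use every collected score and rest on a weaker dropout assumption

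*Protocol article*

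**What the plan says.** The Data analysis section sets out how the intervention effect is examined: "the team will use a t-test and chi-squared test to compare the significance of the intervention-related difference between groups at 6-, 12-, and 18-months". It then adds that "different regression models (ordinary least squares, generalized linear mixed models) will be used for analysis according to the unique circumstances". That choice follows the type of outcome (numerical, binary, categorical), and the knowledge score is the example given of a numerical outcome. The section does not say that scores from several visits enter one model, or which analysis carries the conclusion on knowledge.

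Loss to follow-up appears in the Sample size calculation section: "Assuming a retention rate of 80% during follow-up, 20 participants are needed for each cluster, totaling 3,960 participants for the entire study". There it serves only to enlarge the sample. The Follow-up surveys section schedules the baseline questionnaire again at 6, 12 and 18 months, so each person can contribute up to four knowledge scores. The Primary outcomes section describes the first primary outcome as improvement in knowledge, measured by the baseline and follow-up questionnaires.

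**The concern.** A t-test at month 18 uses only people with a month-18 score, unless missing values are filled in. Someone who answered at baseline, 6 and 12 months and then left contributes nothing to it. Enlarging the sample restores precision but does nothing about who is missing.

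The comparison stays fair if dropout has nothing to do with knowledge, or relates to it in the same way in every arm. It can go wrong if the relation differs by arm. The design gives some reason to consider this. Arms A and B receive biweekly messages, and monthly telephone interviews that probe key knowledge are described only for them. In arm B, 50 of the 100 points that set the doctor's pay come from villagers' understanding. If less knowledgeable people left an intervention arm more readily than control, those remaining would look better than the arm as a whole. Both primary comparisons, intervention against control and A against B, rest on this score.

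**Working it through.** **The plan's own figures.** The section states that "the number of clusters per arm is 66, and the sample size of each arm is 1,056".

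- Completers per village: 1,056 / 66 = 16.
- Enrolled per arm at 80% retention: 1,056 / 0.8 = 1,320.
- Per village: 1,320 / 66 = 20.
- Total: 3 × 1,320 = 3,960.

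These agree with the plan. About 264 people per arm (1,320 − 1,056) are expected to be lost.

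**Does 20% loss bias a per-visit comparison?** This was simulated with 300,000 people per arm, four visits and 20% cumulative dropout. Assumptions not in the protocol: a true effect of 0.30 SD, between-visit correlation 0.4 to 0.8, and a logistic dropout slope of 1 per SD of score. The table gives the estimated 18-month difference in raw scores.

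| Dropout mechanism | Responders at month 18 | Joint estimate from all visits |
|---|---|---|
| Unrelated to score | 0.29–0.30 | 0.29–0.30 |
| Related to score equally in both arms | 0.30–0.31 | 0.30 |
| Related to earlier observed score, one arm only | 0.38–0.45 | 0.30–0.31 |
| Related to the unseen current score, one arm only | 0.42–0.47 | 0.34–0.38 |
| Related to the unseen current score, opposite directions | 0.54–0.63 | 0.37–0.46 |

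So loss alone does not bias the comparison; differential, score-related loss does. The joint estimate removes the bias when dropout depends on observed scores and otherwise leaves 0.04 to 0.16 SD.

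**Does it matter that the outcome is improvement?** Yes. Take a milder setting, again assumed: true effect 0.20 SD, correlation r between 0.5 and 0.7, and loss before month 18 that depends on the 12-month score in one arm only. Let d be the amount by which the mean 12-month score of those retained exceeds that of the whole arm. With normal scores, the retained group's mean shifts by

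- month 18: r(12,18) × d
- baseline: r(12,0) × d
- change from baseline: [r(12,18) − r(12,0)] × d

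With logistic slopes of 0.4 and 0.8 per SD, the raw 18-month difference came out at about 0.24–0.25 and 0.27–0.31. At r = 0.5 the lower figures imply d ≈ 0.04 / 0.5 = 0.08 and 0.07 / 0.5 = 0.14.

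- Equal correlations between all visits: r(12,18) = r(12,0), the shift in change is 0, and the estimate stays at 0.20.
- Correlations that decay, for example 0.5 at one visit apart and 0.25 at two: (0.5 − 0.25) × 0.08 = 0.02 and (0.5 − 0.25) × 0.14 = 0.035, giving about 0.22 and 0.24.
- Dropout that depends on the baseline score: the baseline mean shifts by the full selected amount and month 18 by only a fraction of it, so the terms do not cancel.

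**Clustering.** A plain t-test also ignores the village. With 16 completers per village, the design effect is 1 + 15 × ICC. At an assumed ICC of 0.01 it is 1.15, and at 0.20 it is 4.0. The real two-sided error of a nominal 5% test is 2 × [1 − Φ(1.96 / √design effect)], or about 7% and 33%. A village random effect deals with this.

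**The case against.** The strongest reply is that the protocol does not exclude the better analysis. Generalized linear mixed models are named in the sentence after the tests, and a condensed article may leave the analysis set and missing-data handling to a fuller document. That stands in part. The absence of a missing-data rule is not counted here, and a responders-only analysis is an inference from what a t-test does without imputation, not a rule that the plan states. But the per-visit tests are a stated choice, and the models listed are attached to outcome types, not to the joint use of visits.

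Three stronger readings are tempting, and the protocol does not support them.

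- That dropout will bias the result. No figure shows loss that depends on knowledge differently by arm. Several features work against it: participants are paid for each follow-up questionnaire, doctors in all three arms are rewarded per completed questionnaire, and people planning to leave Liangshan are excluded. Control doctors also set up a village group chat, so the arms do not differ in having one.
- That a joint model would correct any such bias. It does so only if dropout depends on observed scores.
- That the raw-score distortions above, or a false-positive rate derived from them, describe this trial. Shifting a raw 18-month difference by 0.05 SD, with a cluster-adjusted standard error of 0.058 at an assumed ICC of 0.05, gives about 14% in place of 5%. The outcome is described as improvement, for which the shift can vanish, and a plain t-test would not use that standard error.

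**Conclusion.** The point holds as a weakness in a stated method, not as a demonstrated bias. The per-visit tests leave out knowledge scores already collected from people later lost, and without imputation they need dropout to be unrelated to knowledge, or related to it equally in all arms. A model over all visits needs only that dropout depends on observed scores. The size cannot be fixed from the protocol. Under assumed one-arm dependence on earlier scores, the raw-score bias was 0.08 to 0.15 SD on a true 0.30 SD in one setting, and about 0.04 to 0.11 SD on a true 0.20 SD in the milder one. For change from baseline in the milder setting, it was nil with equal correlations and about 0.02 to 0.04 SD with decaying ones. In no scenario was the joint estimate materially worse than the responders-only one, and it was clearly better wherever dropout was differential. The change is worth making.

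**What to change.** For the knowledge outcome, state that the effect analysis is one linear mixed model on all scores from baseline to 18 months, with arm-by-visit terms and random effects for village and person. Read the 6-, 12- and 18-month arm contrasts from it, including A against B, and keep the per-visit tests as descriptive. Say that the model assumes data missing at random. That protection also depends on modelling the correlation between visits adequately: random intercepts alone make it equal for all pairs of visits, so a freer within-person covariance should be allowed if correlations decay.

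The cost is a change of wording and slightly more analysis work. No new data are needed, and mixed models are already named in the plan. The remaining price is reliance on missing at random: if dropout depends on scores that were never observed, bias is reduced but not removed.

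### Villages are randomised, but the named effect tests (t-test, chi-squared, ordinary least squares) ignore the village, so standard errors are too small and false positives exceed 5% once villagers' scores correlate

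*Protocol article*

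**What the plan says.** In the protocol article, Randomization and allocation states: "Randomization is done by the research team at the cluster level using a stratified randomization method". Villages are "randomized into three groups in a 1:1:1 ratio".

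Sample size calculation also treats the trial as clustered. It uses a Stata routine for cluster-randomised trials and reports that "the number of clusters per arm is 66, and the sample size of each arm is 1,056".

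The second paragraph of Data analysis turns to the effect of the messages and says the team will "use a t-test and chi-squared test to compare the significance of the intervention-related difference between groups", at 6, 12 and 18 months. This is separate from the baseline comparison, which has its own sentence in the paragraph before. The section then sorts outcomes into numerical (the knowledge score is the example), binary and categorical, and says that "different regression models (ordinary least squares, generalized linear mixed models) will be used for analysis according to the unique circumstances".

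Nowhere does Data analysis mention village, cluster, a random effect, robust standard errors, cluster-level summaries or an ICC.

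**The concern.** A t-test, a chi-squared test and ordinary least squares with default standard errors all assume independent observations. Here the villagers in one village share the doctor who sends and explains the messages (Study setting and recruitment) and the chat group that doctor creates (Preparation for the intervention). In Intervention B they also share the doctor's pay incentive, which depends on the village's average interview score (Village doctor incentives and performance monitoring). Scores within a village can therefore be expected to correlate.

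If that correlation is ignored, each arm is credited with more information than it holds. This affects the comparison of the intervention arms with control and the knowledge part of the A-versus-B comparison, so both primary outcomes are touched. The A-versus-B contrast is especially exposed, because the thing being compared is applied to the doctor and the village is its natural unit. The same fault carries into all three follow-up times and the subgroup analyses.

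**Working it through.** **Inputs from Sample size calculation.**
- Testing: "two-tailed hypothesis testing is assumed".
- Error rates: "By setting the power = 90%, α = 0.05, and desired confidence level = 95" per cent.
- Size: 66 clusters and 1,056 participants per arm.
- Attrition: "Assuming a retention rate of 80% during follow-up, 20 participants are needed for each cluster, totaling 3,960 participants for the entire study".

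**The plan's own figures.** 1,056 / 66 = 16 evaluable per village. 16 / 0.80 = 20 recruited per village. 66 × 20 × 3 = 3,960. The chain is consistent. The 66 clusters cannot be re-derived, because no effect size, standard deviation or ICC is given.

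**Assumption.** The ICC is not stated, so values from 0.01 to 0.10 are used.

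**Formulas**, with m = 16 per village:
- design effect DE = 1 + (m − 1) × ICC
- naive standard error / true standard error = 1 / √DE
- true two-sided error of a nominal 5% test = 2 × [1 − Φ(1.96 / √DE)]
- effective sample size per arm = 1,056 / DE

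Worked case, ICC 0.05: DE = 1 + 15 × 0.05 = 1.75; 1 / √1.75 = 0.756; 1.96 / √1.75 = 1.48, so the true error is 0.138; 1,056 / 1.75 = 603.

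| ICC | DE | Naive SE / true SE | True type I error | Effective n per arm |
|---|---|---|---|---|
| 0 | 1.00 | 1.000 | 5.0% | 1,056 |
| 0.01 | 1.15 | 0.933 | 6.8% | 918 |
| 0.02 | 1.30 | 0.877 | 8.6% | 812 |
| 0.05 | 1.75 | 0.756 | 13.8% | 603 |
| 0.10 | 2.50 | 0.632 | 21.5% | 422 |

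With no loss to follow-up (m = 20), the error rates at ICC 0.01, 0.02, 0.05 and 0.10 rise to about 7%, 10%, 16% and 25%.

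**Check by simulation** (10,000 null trials per ICC, 66 villages of 16 per arm; proportion significant at 5%):

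| ICC | t-test on individuals | t-test on village means | Chi-squared on individuals |
|---|---|---|---|
| 0 | 0.0504 | 0.0508 | not run |
| 0.01 | 0.0650 | 0.0480 | 0.0675 |
| 0.05 | 0.1386 | 0.0515 | 0.1377 |
| 0.10 | 0.2140 | 0.0495 | 0.2145 |

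The simulation agrees with the formula. A test that respects the village stays near 5%.

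**The case against.** **Mixed models are on the list.** Data analysis names generalised linear mixed models, which could carry a village random effect, and it does not expressly tie ordinary least squares to the knowledge score. Both points are true. But model choice is linked to outcome type and circumstances, not to clustering, and no random effect is named. For a numerical score, least squares is the natural reading. Whichever regression follows, the t-test and chi-squared test remain the stated significance tests.

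**The unit of analysis is not stated.** A t-test on village means would be valid, as the simulation shows, so the individual-level reading is an inference. It is nevertheless the ordinary one: the text mentions no village means, and a standard chi-squared test works on individual counts.

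**An analysis plan not shown may supply the adjustment.** It may. But this is a method stated wrongly, not a detail left out. An analysis plan that corrected it would contradict the protocol.

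**The size is not this trial's error rate.** This stands. The inflation needs an ICC above zero, and its value is assumed. Stratified randomisation would make the formula overstate the inflation if the strata, which are not named, explain between-village variance. In the other direction, Primary outcomes includes family members' scores, which would raise the number of respondents per village and add household correlation.

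**The second primary outcome is partly cost-effectiveness.** This also stands. No test is named for that part, so the finding reaches only its knowledge component.

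**Conclusion.** The concern holds. The trial is randomised and sized by village, but the stated test of the intervention effect takes no account of village, and the one listed method that could do so is left optional. Followed as written, the plan gives standard errors 7% to 37% too small and a true two-sided error of 6.8% to 21.5% for each nominal 5% comparison. These figures assume 16 evaluable participants per village, an ICC between 0.01 and 0.10, and tests run on individuals. At an ICC of zero there would be no inflation, but the shared doctor and chat group make that implausible, and using a cluster-trial sample-size routine presupposes correlation. This must be fixed before analysis, because it bears on the primary comparisons. Leaving the choice of model to circumstances would also allow a clustered or an unclustered result to be picked after the data are seen.

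**What to change.** Replace the effect-test and regression sentences in Data analysis with a firm rule that every between-arm comparison accounts for village, including A versus B and the subgroup analyses.

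- **Knowledge score:** a linear mixed model with a random intercept for village, adding one for household when family members are analysed.
- **Binary and ordinal outcomes:** a generalised linear mixed model, or GEE clustered on village.
- **Acceptable alternatives:** ordinary least squares with village-clustered standard errors, or an analysis of village-level summaries. Choose one in advance for the primary comparisons.
- **Unadjusted t-tests, chi-squared tests and ordinary least squares:** description only.

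The cost is an amendment to the protocol and analysis plan, a few lines of code, and wider, honest intervals. No new data are needed. A sample size from a cluster-trial routine should already have allowed for the wider intervals, though that cannot be confirmed without the ICC and effect size used.
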